### Study design

This is a prospective non-randomized controlled trial. It is a two (group: intervention and control) by three (time: pre-treatment, 5 weeks, 6 months) repeated measures factorial design. The overall study design is illustrated in Fig. 1 and Table 1. In T0 sociodemographic data, medication, and use of previous psychotherapeutic inpatient or outpatient treatments, as well as data on health behavior (e.g. smoking, alcohol consumption, etc.) of the patients will be collected. Participants in the intervention group will complete a comprehensive web-based questionnaire battery at three time points: at the time of admission to the hospital setting (T0), at the end of inpatient treatment five weeks later (T1), and 6 months after discharge from the hospital setting (T2). The control group will accomplish the questionnaire within a time frame of around 6 months after presentation at the Post-COVID Center of the Universitätsklinikum Erlangen (T0), five weeks after T0 (T1), and 6 months after T0 (T2). The questionnaires at T0, T1, and T2 will be made available web-based via a link and a password. Participants who drop out of the intervention or control group will be reported in the final results. Before participation, written informed consent must be given. A schematic overview of the trial flow is given in Fig. 1. The instruments used at each time point are displayed in Table 1.

**Table 1 Tab1:** Overview of the assessment schedule for both groups

Measures	Assessment time points		
	Baseline (T0)	5 weeks later (T1)	6-month follow-up (T2)
Sociodemographic variables	X		
Health behavior	X	X	X
Use of PASC-specific treatments		X**	X
Use of PASC-specific outpatient or inpatient psychotherapeutic treatment	X	X**	X

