#### Inclusion criteria

Aged 18 years or older.Confirmed (e.g. positive PCR or antigen test) SARS-CoV-2 infection and subsequent PASC: complaints that are still present more than 12 weeks after the onset of SARS-CoV-2 infection and cannot be explained otherwise.Written informed consent to participate in the study.Sufficient knowledge of the German language to participate in the study.Treatment group: indication for inpatient psychosomatic treatment due to:

Diagnosis of mental disorder (ICD-10; International Classification of Diseases, 10th Revision).Limitations that significantly reduce the ability to manage everyday life (e.g. the ability to maintain daily structure).and/ or

Subjective stress so great that the quality of life and everyday resilience are significantly limited.

6)Control group: depressive symptoms in self-assessment (PHQ-9 ≥ 10).

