### Control group

The control group will consist of PASC patients for whom there is an indication for inpatient psychosomatic treatment (depressive symptoms in self-assessment: PHQ-9 ≥ 10), but who do not take up the treatment. After group allocation, participants in the TAU condition will have no access to the inpatient psychosomatic treatment, but will not be restrained from using any form of care for PASC-related symptoms. Treatment as usual for PASC patients can entail follow-up contacts with their treating physician or general practitioner, physical training, occupational therapy, or rehabilitation. At T0, T1, and T2, participants of the control group will be questioned about the received psychotherapeutic inpatient or outpatient treatment.

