#### Sample size calculation and statistical methods

Sample size calculation was performed with G*Power Version 3.1.9.7 [71, 72]. The sample size calculation is based on testing the primary hypothesis that inpatient psychosomatic treatment leads to a significantly lower mean PCS Score across the first two follow-up assessments (T1 and T2) as compared to treatment as usual. Because of the novelty of PASC, data on our primary outcome, the PCS Score, were not available in this population over different time points. Therefore, we assumed a conservative correlation of 0.5 among repeated measurements and a medium effect size. Based on a medium effect size (f = 0.25) and a power of 85%, a sample size of 98 participants is required, with 49 participants per group. Assuming a conservative dropout of 20%, we will randomize 118 participants, 58 for each condition.

We will perform standard techniques of data preparation with tests of normality and homogeneity and with imputation of missing data in the case of dropouts. Furthermore, we will conduct different descriptive analyses of sociodemographic and medical data. The primary statistical analyses will be a two-way mixed-design Analysis of Variance (ANOVA) with the independent variables being condition (treatment vs. treatment as usual) and time (T0, T1) and condition by time interaction as fixed effects as well as repeated measures ANOVA for the follow-up measurement with repeated measurements. Additionally, we will perform regression analyses to identify potential predictors of treatment outcomes. In all analyses, two-sided p values of < 0.05 are considered to indicate statistical significance. All analyses will be conducted using the statistical software SPSS.

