### Strengths and limitations

The study’s strengths lie in its robust control design and comprehensive assessment tools. The use of a control group allows for a comparison of outcomes between patients receiving the intervention and those receiving treatment as usual, providing a clearer understanding of the intervention’s effectiveness. Furthermore, the extensive neurocognitive test battery and the detailed measurement of patient-reported outcomes ensure that a wide range of symptoms and impacts are captured. This comprehensive approach allows for a thorough evaluation of the intervention’s effects on both the physical and mental health aspects of PASC. The prior comprehensive interdisciplinary diagnostics in our Post-COVID Center ensure that participants are adequately diagnosed with PASC and have a significant level of psychological distress, making them suitable candidates for psychosomatic treatment.

Despite these promising aspects of this study, several limitations must be considered. One significant limitation is the non-randomized allocation of patients to the control group, which is based on patients’ choice. This self-selection could introduce bias, as those who choose to participate in the intervention may have different levels of motivation or severity of symptoms compared to those who do not. This could potentially affect the generalizability of the study’s findings. Additionally, the study’s reliance on self-reported measures might introduce response bias. Ensuring a large and diverse sample size, along with rigorous statistical analysis, will be crucial in mitigating these limitations.

In conclusion, this study protocol addresses a critical gap in the treatment of PASC syndrome with comorbid mental illnesses. The potential benefits for both health economic factors and patient quality of life are substantial. While limitations such as the non-randomized control group allocation must be acknowledged, the study’s strengths, including its robust design and comprehensive outcome measurements, provide a solid foundation for evaluating the effectiveness of inpatient psychosomatic treatment for PASC. The findings could have significant implications for the broader application of psychotherapeutic interventions in both inpatient and outpatient settings, ultimately contributing to improved care and outcomes for PASC patients.

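### The primary analysis of self-selected groups has no confounder adjustment, and a large sample is wrongly offered as mitigation for self-selection bias

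*Protocol article*

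**What the plan says.** All of the following is from the protocol article.

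- **Allocation.** Strengths and limitations describes a "non-randomized allocation of patients to the control group, which is based on patients’ choice". Control group describes the controls as patients with an indication for inpatient treatment "but who do not take up the treatment".
- **Entry rules (Inclusion criteria).** For one arm: "Treatment group: indication for inpatient psychosomatic treatment due to" an ICD-10 mental disorder, with functional limitation and/or severe subjective stress. No PHQ-9 threshold is set for this arm. For the other: "Control group: depressive symptoms in self-assessment", with PHQ-9 of at least 10.
- **Baseline timing (Study design).** T0 is hospital admission in the intervention group. In the control group it falls "within a time frame of around 6 months after presentation at the Post-COVID Center".
- **Primary analysis (Sample size calculation and statistical methods).** The model is a "two-way mixed-design Analysis of Variance (ANOVA) with the independent variables being condition (treatment vs. treatment as usual) and time (T0, T1", together with the condition-by-time interaction. A repeated measures ANOVA covers follow-up. Regressions are added to look for predictors of outcome, which is a different task from adjusting the group effect.
- **Acknowledged bias and remedy (Strengths and limitations).** "This self-selection could introduce bias, as those who choose to participate in the intervention may have different levels of motivation or severity of symptoms". The answer given is: "Ensuring a large and diverse sample size, along with rigorous statistical analysis, will be crucial in mitigating these limitations".

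**The concern.** The primary hypothesis is superiority to treatment as usual. Without randomisation, the analysis has to carry the defence against confounding, and the model as stated includes none. It uses T0 only as a repeated measure. That protects against group differences that stay constant between T0 and T1, but not against groups that would have changed differently without the programme.

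Choice of treatment, a score threshold in one arm only, and different T0 anchors are all plausible sources of such differential change. The protocol names the bias and then proposes a remedy that does not act on it: a larger sample narrows the interval around a biased estimate. Followed as written, the plan would yield a superiority claim that stays open to confounding by variables the trial already measures.

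**Working it through.** **Inputs.** From the protocol: correlation between repeated measurements ρ = 0.5, f = 0.25, 98 analysed (49 per group), two-sided α = 0.05, 58 per condition recruited. Assumed, because the protocol gives no PCS SD and no group difference: a T0 group difference d of 0.3 or 0.6 SD, shown as a range. No treatment effect throughout.

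**1. The plan's own figure.** For a between-group main effect over m measurements, λ = f²·N·m / (1 + (m−1)ρ), with 1 and N−2 degrees of freedom.
- m = 3: λ = 0.0625 × 98 × 3 / 2 = 9.19, power 85.1%. This reproduces N = 98.
- m = 2: λ = 0.0625 × 98 × 2 / 1.5 = 8.17, power 80.8%. This does not.

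The design has only three time points, so a main effect over three measurements averages T0 in. A stable pre-existing difference then passes into that effect in full. The text speaks of T1 and T2 only, so the inclusion of T0 is inferred from the match.

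**2. The T0–T1 interaction.** With two time points this test is the comparison of change scores. Let the intervention group lie d higher at T0.
- *Stable difference* (still d at T1): difference in change = d − d = 0. No bias.
- *Regressing difference* (ρd expected at T1): difference in change = ρd − d = −(1−ρ)d. For d = 0.3 this is −0.15 SD; for d = 0.6 it is −0.30 SD.

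The standard error is √(2(1−ρ)) × √(2/49) = 1 × 0.202 = 0.202 SD. By the noncentral t, type I error is 11.4% for a bias of 0.15 SD and 31.2% for 0.30 SD. Against the planned effect (d = 2f = 0.5), these biases are 0.15/0.5 = 30% and 0.30/0.5 = 60%. A difference in natural trend of 0.1, 0.2 or 0.3 SD gives 7.8%, 16.5% and 31.2%.

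**3. Does a larger sample help?** With a bias of 0.15 SD, type I error is 11.4% at 49 per group and 12.6% at 58. It rises.

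**4. Does ANCOVA on T0 PCS solve it?** The ANCOVA estimate is the T1 difference minus ρd.
- Regressing: ρd − ρd = 0.
- Stable: d − ρd = +(1−ρ)d, which is 0.15 or 0.30 SD.

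| T0 difference | Change-score type I error | ANCOVA (T0 PCS only) type I error |
|---|---|---|
| Regressing, 0.3 / 0.6 SD | about 11% / 31% | about 5% / 5% |
| Stable, 0.3 / 0.6 SD | about 5% / 5% | about 13–14% / 37–38% |

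(ANCOVA entries by simulation, 49 per group.) Each method is unbiased where the other is biased, and the two biases have opposite signs.

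**5. Threshold in one arm only.** In a simulation, only the controls were selected (top 30–50%) on a fluctuating score correlated 0.4–0.6 with T0 PCS and half as strongly with T1. The change comparison is biased by 0.16–0.35 SD, with type I error 12–40%; ANCOVA on T0 PCS gives 4.7–5.2%. If the score also predicts T1 beyond T0 (0.6 with T0, 0.45 with T1), ANCOVA on T0 PCS alone still rejects in 11–18%. More than the T0 PCS Score would then have to be adjusted for. All these correlations are assumptions.

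**The case against.** **Stable differences cancel.** A reader might infer that every baseline difference feeds straight into the primary effect. For the T0–T1 interaction that is wrong: time-constant effects of severity, illness duration or prior therapy drop out. This part of the objection stands, and it limits the point to differential trend, regression to the mean, and any main effect that includes T0.

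**ANCOVA is not simply better.** A reader might conclude that the mixed ANOVA should give way to ANCOVA, perhaps expecting a gain in power too. Step 4 shows that ANCOVA on T0 PCS has a matching bias when the difference is stable, and the documents do not say which case applies. A power gain presumes covariates balanced between the groups, which is in doubt here.

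**No direction can be claimed.** A reader might suppose that intervention patients enter when their symptoms are at their worst. The protocol says only that T0 is at admission. Controls regressing from a high PHQ-9 would bias against the programme. The interval from presentation to admission is not given either, so the control group's T0 timing shows a different anchor, not a known gap. PHQ-9, itself a secondary outcome, could regress in the controls, but the screen is undated and the source distribution unknown, so no size can be attached.

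**The arms share more than the entry rules suggest.** Both come from one centre with the same diagnostic work-up, and the control threshold is meant to represent the same indication. That is so, but the operational criteria still differ.

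**Detail belongs in an analysis plan.** Covariate lists often do. Here, however, the protocol fixes the primary model and its terms, names the bias, and states a remedy that is partly wrong. Those are statements in the document, not omissions.

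**Conclusion.** The point holds in a limited form. Self-selected groups with different entry rules and T0 anchors are compared by a model without confounder adjustment, and sample size is wrongly presented as mitigation. Time-constant additive differences are handled by the T0–T1 interaction; differential trend and regression to the mean are not. A between-group main effect that includes T0 carries a stable pre-existing difference in full.

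Size and direction are unknown. The figures of 0.15 to 0.30 SD and 11% to 31% type I error are illustrations. They rest on the protocol's assumed correlation of 0.5, 49 per group, and an assumed T0 difference of 0.3 to 0.6 SD that regresses. They do not show that the result will be biased by that much, or in favour of the programme. What the documents do support is that neither a positive nor a null result from the stated model alone could be safely attributed to the programme.

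**What to change.** 1. Pre-specify a confounder-adjusted estimate of the condition effect on PCS at T1, and likewise at T2, by covariate adjustment or by propensity (overlap) weighting. Use variables collected at T0: PCS Score, PHQ-9, GAD-7, FSS, age, sex and prior psychotherapy. Add time since infection only if it is captured; it is not named in Table 1 or in the T0 list under Study design.
2. Report this estimate beside the condition-by-time result, and state in advance that superiority is concluded only if the two agree. Each is biased under a different assumption about the T0 difference.
3. Add a sensitivity analysis restricted to patients with T0 PHQ-9 of at least 10 in both arms.
4. Replace the sentence in Strengths and limitations on sample size. Say that adjustment addresses measured confounding only, and that unmeasured confounding, for example by motivation, remains.

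**Cost.** With covariate adjustment, seven covariates take about 7 degrees of freedom (8 with time since infection) out of 98 − 2 = 96. There is some extra analysis, and requiring agreement makes superiority harder to claim. No new data are needed for the listed variables; whether time since infection is recorded needs confirming.

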**Methods and analysis:**

This study presents a non-randomized controlled trial aimed at evaluating the effectiveness of a five-week multimodal inpatient psychosomatic treatment program for individuals experiencing PASC symptoms and comorbid mental illness. A total of 118 patients presented at the Post-COVID Center at the Universitätsklinikum Erlangen will be assigned to the intervention group receiving inpatient psychosomatic treatment or the control group receiving treatment as usual. The inclusion criteria for the intervention group are a diagnosis of PASC and at least one condition of mental distress and problems with coping with illness. The primary objective of the intervention is to reduce mental ailments, including depression and anxiety, as well as neurocognitive deficits, and to address PASC symptoms such as fatigue and pain. The core elements of the treatment are psychotherapy in individual and group settings, medical treatment, neurocognitive training, and physical therapy, adapted to the individual’s capacity and oriented towards the concept of pacing. After enrollment, participants will undergo a 6-month follow-up to assess long-term results and the sustainability of the intervention effects.

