### Primary hypothesis

We expect the intervention to be superior to treatment as usual (TAU) regarding a significantly lower mean of PASC symptoms measured by the Post-COVID Syndrome Scale (PCS Score) post-treatment and at 6 months follow-up.

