### Outcomes

#### Primary outcome

The primary outcome are symptoms of PASC at the end of the treatment (T1, see Table 1). To measure those, we will use the PCS-Score. The PCS-Score consists of 12 yes/no questions and covers the entire spectrum of possible PASC symptoms. Each question is given its weighting factor, which assigns a meaning to the corresponding symptom complex. The resulting sum score ranges from 0 (= complete absence of any symptoms) to 59 (= presence of symptoms in each of the 12 symptom complexes). A clinically relevant PASC can be assumed from a PCS Score of 26.25 (high PCS Score). Values between 10.75 and 26.25 indicate an intermediate or moderate PASC. The PCS Score was validated on a German population [48].

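### The 6-month part of the primary hypothesis is not tied to a test at T2, and most readings of the follow-up ANOVA can be significant when the effect has gone by then

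*Protocol article*

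**What the plan says.** All references are to the protocol article.

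- **Primary hypothesis:** the intervention is expected to give a "significantly lower mean of PASC symptoms measured by the Post-COVID Syndrome Scale (PCS Score) post-treatment and at 6 months follow-up".
- **Abstract, Methods and analysis:** "participants will undergo a 6-month follow-up to assess long-term results and the sustainability of the intervention effects".
- **Primary outcome:** the time point is the end of treatment: "The primary outcome are symptoms of PASC at the end of the treatment (T1, see Table 1".
- **Study design:** "It is a two (group: intervention and control) by three (time: pre-treatment, 5 weeks, 6 months) repeated measures factorial design".
- **Sample size calculation and statistical methods:** the sample size rests on a "significantly lower mean PCS Score across the first two follow-up assessments (T1 and T2) as compared to treatment as usual". The primary analyses are a mixed ANOVA with "time (T0, T1) and condition by time interaction as fixed effects", "as well as repeated measures ANOVA for the follow-up measurement with repeated measurements".

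For the T0/T1 ANOVA the article names the time levels and the interaction. For the follow-up ANOVA it names neither, and it gives no comparison of the groups at T2.

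**The concern.** A hypothesis of superiority at 6 months has a specific null: no group difference at T2. An omnibus F test over several time points has a different one.

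If the condition-by-time interaction over T0, T1 and T2 decides, the null is that the two profiles are parallel. That null is false whenever the groups diverge at any time point, including at T1 only. If the group main effect over the three times decides, the null is equal average level, and the average includes the pre-treatment value.

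The T0/T1 ANOVA already covers the end of treatment, so the follow-up test is what has to carry the 6-month statement. If its result can be driven by T1 alone, a significant result says little about whether any benefit remains at 6 months, which is the stated purpose of the follow-up.

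**Working it through.** **Inputs from the article (sample size section):** f = 0.25, power 85%, two-sided alpha 0.05, correlation ρ = 0.5, and 98 analysable participants, so n = 49 per group. For two equal groups d = 2f = 0.5.

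**Assumptions not in the article:** the group differences at (T0, T1, T2), in SD units, are (0, 0.5, 0) for a vanished effect and (0, 0.5, 0.5) for a sustained one. There is no baseline difference, and variances and correlations are equal.

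**1. The plan's own figure.** For the between-group effect in a repeated measures ANOVA with m measurements, λ = f²·N·m / (1 + (m−1)ρ), with 1 and N−2 df.
- m = 3: λ = 0.0625 × 98 × 3 / 2 = 9.19, power 85.1%. The smallest even N reaching 85% is 98, so the figure is reproduced.
- m = 2: λ = 0.0625 × 98 × 2 / 1.5 = 8.17, power 80.8%; 110 would be needed.
- Within-between interaction at the same f: 38 (m = 2) or 32 (m = 3).

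The 98 therefore corresponds to a group main effect over three measurements.

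**2. Formulas for the follow-up test.** With group differences d_j and mean difference d̄:
- interaction: λ = (n/2)·Σ(d_j − d̄)² / (1−ρ), with (m−1) and (2n−2)(m−1) df;
- group main effect: λ = (n/2)·d̄² / [(1 + (m−1)ρ)/m], with 1 and 2n−2 df.

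**3. Three-time interaction.**
- Vanished effect: d̄ = 1/6, Σ = 1/36 + 4/36 + 1/36 = 1/6, λ = 24.5 × (1/6) / 0.5 = 8.17 with 2 and 192 df. It rejects in 72.0% (simulated 71.7%, 20,000 trials).
- Sustained effect: d̄ = 1/3, Σ = 4/36 + 1/36 + 1/36 = 1/6, so λ is again 8.17 and it rejects in 72.0% (simulated 71.8%).

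The two patterns have the same noncentrality, so this F test cannot tell them apart.

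**4. All readings, effect vanished at T2 (d = 0.5 at T1).**

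| Deciding term | λ | Rejects |
|---|---|---|
| Interaction, T0/T1/T2 | 8.17 | 72.0% |
| Interaction, T1/T2 | 24.5 × 0.125 / 0.5 = 6.13 | 68.8% |
| Group main effect, T1/T2 | 24.5 × 0.0625 / 0.75 = 2.04 | 29.3% |
| Group main effect, T0/T1/T2 | 24.5 × (1/36) / (2/3) = 1.02 | 17.0% |
| Interaction, T0/T2 | 0 | 5.0% |

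The T1/T2 interaction has a further fault: its null is an equal group difference at T1 and T2, which is true when the effect is fully sustained.

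**5. Sensitivity of the three-time interaction (vanished effect).** At ρ = 0.5: 31% for a T1 effect of 0.3 SD, 52% for 0.4, 87% for 0.6, 99% for 0.8. At 0.5 SD: 56% for ρ = 0.3 and 92% for ρ = 0.7. With 58 per group, 0.5 SD and ρ = 0.5: 79.6%.

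**6. Power of a T2 contrast, sustained 0.5-SD effect.** For the difference in T0-to-T2 change, λ = 24.5 × 0.125 / 0.5 = 6.13, power 68.8% (simulated 68.5%), against 72.0% for the three-time interaction. For T2 adjusted for T0, the residual variance is 1 − ρ² = 0.75, so λ = 24.5 × 0.25 / 0.75 = 8.17 with 1 and 95 df, power about 81%.

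**The case against.** The strongest reply is that the three-time interaction is inferred. The follow-up sentence states no time levels, and the two-by-three description concerns the assessment design rather than this model. An ANOVA on T0 and T2, built like the one on T0 and T1, is an available reading and would hold 5%. The sample size points to a group main effect, for which the rate is 17% or 29%. The article gives no T1-only effect pattern and no rule that a significant omnibus F alone establishes a 6-month benefit. The choice of contrast may also be settled in an analysis plan that is not shown.

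Much of this stands. A reader might infer that the plan will test the 6-month hypothesis over all time points, and that a vanished effect would be declared significant in most trials. The document does not support that without conditions. It names neither the levels nor the term, and even under the interaction reading the rate is 31% at 0.3 SD and about half at 0.4 SD.

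The reply does not remove the point. The article itself places the follow-up ANOVA among its primary analyses and sets it beside a hypothesis about 6 months. Of the five readings examined, four exceed 5% for that hypothesis. The one that does not is nowhere stated. An analysis plan that followed this sentence literally could carry the mismatch forward.

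**Conclusion.** The point holds in conditional form. The 6-month part of the primary hypothesis has no test aimed at T2. If the condition-by-time interaction over the three times decides, a 0.5-SD effect at T1 that has vanished by T2 is significant in about 72% of trials, as often as a sustained one. If a group main effect decides, the rate is about 17% (three times) or 29% (T1 and T2). A T0/T2 interaction would be sound.

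These rates rest on the assumed effect pattern, no baseline difference, equal correlations and 49 per group. The primary outcome is set at T1 and has its own ANOVA, so the weakness affects the 6-month claim and not the end-of-treatment result. It should be corrected before analysis.

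**What to change.** In the statistical methods section, name a 1-df between-group contrast at T2 as the test of the 6-month hypothesis, with its 95% confidence interval. Use either the group difference in PCS Score change from T0 to T2 or the difference at T2 adjusted for T0, and choose one in advance, because the two can differ when groups differ at baseline. State that a 6-month or sustained effect is claimed only if this contrast favours the intervention, and that the omnibus F is descriptive.

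The cost is a few lines of text and one contrast in SPSS, with no new patients or data. As a change score the contrast has slightly less power for a sustained 0.5-SD effect (about 69% against 72%). The baseline-adjusted form loses none under the same assumptions.

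The contrast does not remove the self-selection that the article acknowledges under Strengths and limitations. Nor does it remove the difference in T2 timing under Study design: six months after discharge in the intervention group, six months after T0 in the control group. Both should be stated beside the 6-month result.
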